### Sample size calculation

The sample size will be calculated for the baseline cross-sectional analysis of this study. The sample size is determined using single proportion formula [41] for estimating prevalence. Based on the proportion of adolescents who were obese in Kuala Lumpur, Malaysia (15.8%) [14], with the desired level of confidence at 95% and desired level of precision of 0.05, a minimum of 204 subjects are required for the study. In consideration of the non-response rate and attrition rate among adolescents, the sample size is increased (+ 25%) to 256 adolescents.

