##### Physical activity and fitness level

Physical activity level will be assessed subjectively using the physical activity questionnaire for older children (PAQ-C) [45]. The Malay version of PAQ-C had been validated among adolescents aged 10–17 years old [46]. A total of 10 items are assessed in the PAQ-C to assess the general levels of physical activity of adolescents over the past seven days and will be scored based on a 5-point scale ranging from ‘no activity’ (1), and ‘7 times or more’ (5). The mean total physical activity score will be calculated and classified into low (1–2.33), moderate (2.34–3.66), and high (3.67–5) [47]. Additionally, screen time such as watching television, using a computer, and playing video games of an adolescent during weekends and schooling days will be assessed as well and further classified into screen time less than two hours and more than two hours [14].

In addition, a subsample of 50 adolescents will be randomized for objective measurement of physical activity level using a pedometer (YAMAX Digi-Walker SW-700) [48]. Adolescents are assigned a pedometer, elastic belt, and a 4-day pedometer diary. The pedometer will be distributed on the same day of data collection and adolescents are instructed to self-monitor their physical activity for four consecutive days with at least one weekend day [49] by wearing the pedometer at the waist from the time they wake up until they go to bed at night, excluding water-based activities and bathing time. Subjects are requested to record the day-end values for pedometer steps, other readings displayed, and non-ambulatory activities (e.g., swimming, cycling, etc.) and to reset to zero every day. A reminder will be sent to the subjects or their parents/guardians at least once throughout the data collection period.

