##### Anthropometric measurements

All equipments will be calibrated before the measurements are performed. The body height of subjects will be measured using a calibrated vertical stadiometer (Seca 213 portable stadiometer, SECA GmbH & Co., KG. Hamburg, Germany), whereas weight and body fat percentage will be measured using the Bioelectrical Impedance Analyzer (OMRON HBF-375 Karada Scan Body Composition Monitor, OMRON HEALTHCARE Co., Kyota, Japan). Both height and weight measurements are recorded to the nearest 0.1 cm and 0.1 kg, respectively. The nutritional status of adolescents will be determined based on Z-scores for height-for-age (HAZ) and BMI-for-age (BAZ) of WHO growth reference 2007 for adolescents between 5 and 19 years old using WHO AnthroPlus version 1.0.3 software (WHO, Geneva, Switzerland). The classification as followed, stunting (HAZ < -2SD), normal height (HAZ > -2SD), thinness (BAZ < -2SD), normal weight (−2SD ≤ BAZ ≤ +1SD), overweight (+1SD < BAZ ≤ +2SD), and obesity (BAZ > +2SD) [59]. The body fat percentage will be classified using percentile scores for sex and age based on the findings by McCarthy et al. [60] into underfat (<2nd percentile), normal (2nd – 85th percentile), overfat (>85th – 95th percentile), and obese (>95th percentile).

Waist circumference will be measured at the midway between the lowest rib and the superior border of the iliac crest as recommended by WHO [61] using a non-elastic SECA 201 Ergonomic circumference measuring tape (DECA GmbH & Co., Hamburg, Germany) to the nearest 0.1 cm. A cut-off point of the 90th percentile of waist circumference percentile classification for Malaysian children and adolescents [62] will be used to identify abdominal obesity. For adolescents aged 17 years and above, WHO/IASO/IOTF (2000) for Asian cut-off [63] will be used instead. Abdominal obesity was defined as ≥90 cm for men and ≥ 80 cm for women. Mean average values will be used for data analysis.

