##### Anaemia status assessment

A haemoglobin level test will be performed to identify the anaemia status of each adolescent by using the HemoCue haemoglobinometer (HemoCue® Hb 201+ System, Angelholm, Sweden), point-of-care testing on capillary blood samples. Anaemia status and level of severity are determined according to the age and gender-specific haemoglobin cut-off point as defined by WHO [64]: (i) < 115 g/L for 5 to 11 years of age; (ii) < 120 g/L for 12 to 14 years of age and non-pregnant women (15 years of age and above); (iii) < 130 g/L for men (15 years of age and above).

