### Data management and analysis

Data analysis will be performed using IBM SPSS 25.0 (SPSS Inc., Chicago, IL, USA). A test of normality will be performed using a skewness value (between − 2 and + 2) for the continuous variables. The univariate analysis will be used to report descriptive data including mean score, median, and standard deviation for continuous variables and percentage and frequencies for categorical variables. Independent-samples *t*-test and One-way ANOVA will be used to compare differences between groups for continuous variables and chi-square analysis will be conducted to examine associations for categorical variables. Correlation test will be used to see if correlation exist between variables. A paired-samples *t*-test will be conducted to determine the statistical differences between the two monsoon seasons. Logistic regression will be performed separately for seasons to determine the relationship between nutritional status and selected variables (Food security, lifestyle factors and neighbourhood environment factors). The Generalized Linear Mixed Model will be used to determine the seasonal effects on food security, lifestyle factors, neighbourhood environmental factors, and its effects on nutritional status. The significance level for all analyses is set at *p* < 0.05.

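### The only per-season regression named for nutritional status is logistic; adding linear models of BAZ, HAZ and haemoglobin would recover information at almost no cost

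*Protocol article*

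**What the plan says.** Under Data management and analysis, the protocol article states: "Logistic regression will be performed separately for seasons to determine the relationship between nutritional status and selected variables". The factors are food security, lifestyle and neighbourhood environment. It does not say which measure of nutritional status is the outcome, or whether the outcome is binary, ordinal or multinomial. No linear regression of a nutritional measure is named.

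The same section also names t-tests and ANOVA for continuous variables, a correlation test, a paired t-test between seasons, and a Generalized Linear Mixed Model (GLMM) that covers effects on nutritional status. No distribution or link is given for the GLMM.

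The measurements are continuous at source. Under Anthropometric measurements, nutritional status rests on HAZ and BAZ z-scores. HAZ is then split at −2 SD, and BAZ into four ordered classes. Under Anaemia status assessment, "A haemoglobin level test will be performed to identify the anaemia status of each adolescent", with one haemoglobin cut-off listed per age and sex group.

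Under Sample size calculation, the target comes from an obesity proportion of 15.8%, a "desired level of confidence at 95% and desired level of precision of 0.05", and so "a minimum of 204 subjects are required for the study", raised by 25% to 256. No power is stated for any association.

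**The concern.** A binary outcome treats adolescents on either side of a cut-off as different and everyone on the same side as alike. The WHO cut-offs are needed to report prevalence. Nothing in the document says that the association analysis must use them alone, and no reason is given for using only a categorical outcome.

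The sample was sized for the precision of a prevalence, so the per-season associations have no power to spare. A yes/no obesity outcome would have about 32 to 40 events for a list of factors that could be long. The risk is that a moderate association is reported as absent, or appears in one monsoon season and not the other by chance, when the values already collected could have shown it.

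**Working it through.** **Inputs from the document:** obesity proportion 15.8%, precision 0.05, 95% confidence, n = 204 and 256, significance level 0.05. **Assumptions:** two-sided tests, a normally distributed outcome, one standardised continuous factor, a straight-line relation with correlation r, and no clustering in either model. The protocol gives no effect size.

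**1. The plan's own figure.** n = 1.96² × 0.158 × 0.842 / 0.05² = 204.4, and 204.4 × 1.25 = 255.5. The stated 204 and 256 reproduce within rounding.

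**2. Events under yes/no coding.** 204 × 0.158 = 32.2 and 256 × 0.158 = 40.4. The 256 already contains the allowance for non-response and attrition, so 40 at follow-up would require no loss.

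**3. Information kept by a cut.** For a normal outcome cut at prevalence q, relative efficiency is φ(z)² / [q(1 − q)], where z is the cut point. At q = 0.158, z = 1.003 and φ(z) = 0.2413, so 0.2413² / 0.1330 = 0.438. Then 204 behaves like about 89 and 256 like about 112.

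| Prevalence at the cut | Information kept | Lost |
|---|---|---|
| 5% | 22% | 78% |
| 10% | 34% | 66% |
| 15.8% | 44% | 56% |
| 20% | 49% | 51% |
| 30% | 58% | 42% |
| 50% | 64% | 36% |

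The loss passes one half at a prevalence of about 21%.

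**4. Power at 15.8%.** Outcomes were simulated as y = r·x + √(1 − r²)·e. A linear test on y was compared with a logistic Wald test on y above the cut. Ranges show separate simulation runs.

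| r | n | Linear | Logistic |
|---|---|---|---|
| 0.15 | 204 | 59% | 30% |
| 0.20 | 204 | 82–84% | 45–46% |
| 0.25 | 204 | 95% | 68% |
| 0.15 | 256 | 69% | 35% |
| 0.20 | 256 | 90–91% | 54–59% |

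At r = 0.20 and n = 204, logistic power is about 25% if the prevalence is 5% and about 58% if it is 30%.

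**5. Two-group version.** With half the sample exposed and n = 204, a shift of 0.39 SD gives 80% power on the continuous scale. As obese yes/no (11.2% against 20.4%), power is 44%. With 30% exposed and a shift giving 80% on the continuous scale, it is 50%.

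**6. Ordered BAZ classes.** With k classes, information kept is the sum over classes of (φ at the lower limit − φ at the upper limit)² / class share. Taking 15.8% obese, and assuming 5–10% thin and 12–18% overweight, four ordered classes keep about 74–83%.

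**7. A factor that widens both tails.** If the SD of BAZ is multiplied by exp(0.2x) with no shift in the mean (an assumption), linear power is about 5–7% and logistic power 41–45% at n = 204. At n = 256 the figures are about 6% and 54–55%. Here the logistic model does better.

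**The case against.** The strongest reply is that the plan is less restrictive than it looks. Four parts of it stand:

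- Yes/no coding is an inference. Logistic regression includes ordinal and multinomial forms, and BAZ has four ordered classes. An ordinal model would remove most of the loss for BAZ.
- The section names correlation tests, t-tests and ANOVA, all of which can use the continuous values, although unadjusted. The GLMM could also use them; its outcome scale is simply not stated.
- The WHO classes are clinically meaningful, and the study concerns malnutrition at both ends. A factor that raises both thinness and obesity would be missed by a linear BAZ model (step 7), and a quadratic term would not repair this, because the change is in the spread and not the mean.
- No study objective is expressly tied to the per-season logistic models.

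A reader might therefore infer stronger claims that the document does not support. It does not show that continuous data are discarded throughout the plan. It does not show that power is halved for every outcome: the 56% loss belongs to obesity at 15.8%, and the prevalences of stunting, anaemia and overweight-or-obese are not given. It gives no ground for demoting the logistic models. Nor does it show that screen time is dichotomised in any model: Physical activity and fitness level says only that it is "further classified into screen time less than two hours and more than two hours", not that the class replaces hours.

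What the reply does not remove is that no adjusted per-season model of the continuous values is named, and that the GLMM as described cannot be relied on to fill the gap.

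**Conclusion.** The point holds in limited form, as an inexpensive improvement; no stated figure is wrong. Logistic regression is the only per-season analysis named that can adjust the factors for one another, although three central measures are continuous. If obesity is coded yes/no at 15.8%, about 56% of the information in BAZ is lost, and at r = 0.20 power falls by roughly 36 to 38 points at n = 204 and 31 to 37 points at n = 256.

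These figures rest on assumed correlations, normality, a straight-line relation and binary coding. The loss is greater for rarer outcomes, below half above about 21% prevalence, and about 17–26% for four ordered BAZ classes under the assumed shares. For a factor acting on both tails, the logistic model is the better one. That is why the two sets of models belong side by side.

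**What to change.** In Data management and analysis:

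1. Add per-season linear models of BAZ, HAZ and haemoglobin on the same food security, lifestyle and neighbourhood factors.
2. State that the GLMM for these three outcomes uses a Gaussian distribution with identity link.
3. Keep the logistic models for the WHO classes alongside, state how each outcome is coded, and model thinness and overweight/obesity separately without pooling them.

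The cost is wording and a few more models to report. Weight, height and haemoglobin are already scheduled in both seasons (Table 1), so no new data are needed. Mean shifts in z-score are less direct for policy readers than odds ratios, which the retained logistic models supply. The article reports that the data had not been processed for analysis at submission, so at that point the change could be made without sight of results.

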### The status and timeline of the study

The first adolescent was enrolled on the 1st of November 2021. The recruitment process and baseline data collection were completed on the 30th of April 2022. At the time of submission, all de-identified subjects data are kept and manage but have not yet been processed for analysis.

## Discussion

This study is intended to provide a detailed seasonal analysis of changes in nutritional status and its associated factors, including food security, lifestyle-related and neighbourhood environmental factors of urban poor adolescents in Kuala Lumpur, Malaysia. The valuable findings of this study hoped to enlighten and enable relevant stakeholders, including policymakers and the government sector to better understand the seasonal nature of malnutrition in Malaysia and to seize appropriate programme and policy opportunities that are seasonally sensitive, effective, and sustainable in addressing multiple challenges to combat all forms of malnutrition, also known as double-duty actions for nutrition. Information gathered in this study may be also useful in the future prediction of possible outcomes in relation to the seasonal variation and climate changes in the region. On the other hand, this study will also provide insights into household food security, diet quality, physical activity, and physical fitness levels of urban poor adolescents, which can be used as references in the formulation of future nutrition initiatives to improve nutrition and health status of urban poor communities in Malaysia. Evidence-based nutrition recommendations could aid in strengthening existing policies and measures that are relevant to adolescent nutrition by promoting healthy dietary habits and physical activity while also increasing resilience to food insecurity.

This present study has several strengths as this is the first study that examines the underlying factors of malnutrition that are subjected to seasonality and affecting the nutritional outcomes of urban poor adolescents. Assessments at both time points across the monsoon allow the assessment of the change in nutritional status and associated factors. Multiple assessments of nutritional status, including weight status, body composition, and haemoglobin status, could provide a more comprehensive understanding of the nutritional status of urban poor adolescents, which these data are scarce among the urban poor population in Malaysia. Besides, using both objective (spatial) and subjective (perceived) assessments to assess the food and built environment provides a complete picture of the residential neighbourhood environment of the urban poor. In addition, a better understanding of both physical and perceived food and the built environment surrounding urban poor communities could help to develop an effective system approach that mitigates neighbourhood environmental consequences of malnutrition by ensuring universal access to healthy food sources and supporting infrastructure in the urban poor areas.

In terms of limitations, the study results may not be representative of the general population of adolescents in Malaysia as this study is designed to focus only on the urban poor adolescents who are residing in low-cost high-rise flats in Kuala Lumpur, Malaysia. A nationwide study could be implemented in a different residential setting to ensure the generalizability of the study outcome. Besides, since the study is being conducted during the COVID-19 pandemic period, which could increase drop-out rates. To address these issues, researchers will ensure that the data collecting process complies with the standard operating procedure (SOP) that has been established by relevant authorities while also thoroughly explaining the data gathering process to parents and adolescents. Moreover, additional effects of the COVID-19 pandemic on the study variables, such as food security status, financial status, food environment, and diet may have been overlooked in this study, requiring further investigation.

## Data Availability

Data analyzed or generated in the study will be available upon reasonable request from the corresponding author.

## Abbreviations

ANOVA: Analysis of Variance
BMI: Body Mass Index
DBKL: Kuala Lumpur City Hall (*Dewan Bandaraya Kuala Lumpur*)
EBQ: Eating Behaviours Questionnaire
GIS: Geographic Information System
HLPE: High-Level Panel of Experts
MOH: Ministry of Health Malaysia
NEMS-P: Perceived Nutrition Environment Measures Survey
NPANM: National Plan of Action for Nutrition of Malaysia
PA/PPR: People Housing Programme (*Perumahan Awam/ Program Perumahan* Rakyat)
PAQ-C: Physical Activity Questionnaire for Older Children
PANES: Physical Activity Neighbourhood Environmental Survey
PDS: Pubertal Development Scale
SDG: Sustainable Development Goals
S-MHEI: Standardized Malaysian Healthy Eating Index
UN: United Nations
USDA: United States Department of Agriculture
WHO: World Health Organization
